# Substudy 2: Prospective observational study on maternal and neonatal morbidity in pregnant women with COVID-19

## Objective/s

1. Determine the variables that are associated with more maternal and neonatal morbidity.
2. Characterize the clinical course of SARS-CoV-2 infection during pregnancy (for example, severity of maternal symptoms, distribution of gestational age at onset, ICU admission, mechanical ventilation, death).
3. Identify additional risk factors and risk modifiers (e.g., symptomatic infection, SARS-CoV-2 positive amniotic fluid, co-infections).

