## Study design

Prospective observational registry study of pregnant women with suspected SARS-CoV-2 infection at any time during pregnancy with positive test results for SARS-CoV-2.

A specific database will be developed, which will include the baseline characteristics of the pregnant women, aspects related to the course of pregnancy and childbirth, and the new-born. Vertical transmission will be analysed only by means of a nasopharyngeal swab from the new-born before contact with the mother. This registry sets an observation deadline of up to 14 days after birth for the new-born and 6 weeks postpartum for the mother. The registry will be hosted on a secure https server, this server will be physically located at **OBS Covid Spain** of the company ReserArch which has a contract with the Puerta de Hierro-Majadahonda University Hospital Research Foundation.

Recruitment period will be between 1st March 2020 and 1st March 2021.

After that, different sub-analyses will be carried out with the data extracted in the registry and the secondary objectives will be addressed.

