## Study population and selection criteria

For the characterization of the clinical course of SARS-CoV-2 infection during pregnancy, the pre-study sample size calculation has not been carried out, as registry-based studies generally tend to be comprehensive without involving hypotheses.

Patients eligible for follow-up of target population will be any pregnant woman who is suspected or needs to be ruled out as having a SARS-CoV-2 infection at any time during pregnancy with positive test results for SARS-CoV-2 by PCR.

Information regarding each pregnant woman's demographic characteristics, comorbidities and current obstetric history was extracted from the medical history and the patient interview; subsequently, age and race were categorized according to the classification used by the Center for Disease Control and Prevention (CDC) (17).

For the selection of the control group to be collected in the same database, patients with a negative COVID-19 delivery diagnosed by PCR screening at delivery, or less than 3 days before, were considered.

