## Patients

Patients eligible for follow-up or target population will be any pregnant woman who is suspected of or needs to be ruled out as having SARS-CoV-2 infection at any time during pregnancy with positive test results for SARS-CoV-2 by PCR.

The result in the PCR test on a sample of nasopharyngeal and/or oropharyngeal swab was considered synonymous with exposure/non-exposure, defining a case as any pregnant woman with a positive result, regardless of the symptoms. Those cases with clinical presentation of COVID19 were classified according to the WHO division for adults into: mild symptoms, mild-moderate pneumonia, severe pneumonia and septic shock (16).

The recommended samples for diagnosis are samples from the upper respiratory tract: nasopharyngeal and/or oropharyngeal swab.

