## Primary variables

|                                                    |                                      |
|----------------------------------------------------|--------------------------------------|
| Age                                                | Premature rupture of membranes (PRM) |
| Race                                               | Preterm PRM                          |
| Weight at the beginning of pregnancy               | NICU admission                       |
| BMI: Body Mass Index                               | NICU admission days                  |
| Single or Multiple Gestation                       | APGAR 5                              |
| IVF with egg donation and IVF without egg donation | Arterial pH                          |
| Medical comorbidity                                | Postpartum haemorrhage               |
| Blood group and Rh                                 | Abruptio placentae                   |
| Maternal mortality                                 | Severe preeclampsia                  |
| ICU admission                                      | HELLP                                |
| Intrauterine foetal mortality                      | Pulmonary embolism                   |
| COVID 19 diagnosis date                            | Endometritis                         |
| Delivery < 37 weeks                                | Mastitis                             |
| Delivery Type                                      |                                      |

|                                                   |                                 |
|---------------------------------------------------|---------------------------------|
| COVID-19 symptoms                          |                                 |
| Mild symptoms (Symptoms reported at birth) | Cough                           |
|                                                   | Fever                           |
|                                                   | Dyspnoea                        |
|                                                   | New olfactory or taste disorder |
|                                                   | Fatigue/malaise                 |
|                                                   | Altered consciousness           |
|                                                   | Headache                        |
|                                                   | Nausea/vomiting                 |

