### Safety Measures and Confidentiality

Protection of human subjects: Pregnant women and newborns participate in the registry as mentioned above. No biological samples are collected for specific analysis in this study.

The laboratory tests collected in the registry will be those carried out in each site according to its protocol. No extra lab tests will be carried out for this study and there is no handling of biological tests. The data collected through the national registry for SARS-CoV-2 in pregnancy does not contain personally identifiable information.

The data of the subjects included in it will be treated in accordance with Organic Law 3/2018, of 5th December, on the Protection of Personal Data and guarantee of digital rights.

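### Substudy 2 pools cases found on suspicion during pregnancy with cases that screening at delivery can add, so its timing and outcome percentages partly reflect when women were tested

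*Protocol*

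**What the plan says.** **Target.** Substudy 2, Objective/s, sets out to characterise the clinical course of infection in pregnancy and gives as examples how severe the mother's symptoms are and the "distribution of gestational age at onset, ICU admission, mechanical ventilation, death".

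**Cases.** Substudy 2, Patients, takes "any pregnant woman who is suspected of or needs to be ruled out as having SARS-CoV-2 infection at any time during pregnancy" who has a positive PCR, "defining a case as any pregnant woman with a positive result, regardless of the symptoms". The general Study design section says the same: "pregnant women with suspected SARS-CoV-2 infection at any time during pregnancy with positive test results for SARS-CoV-2".

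**Testing.** Testing follows local practice: "No extra lab tests will be carried out for this study" (Safety Measures and Confidentiality). No systematic testing earlier in pregnancy is described.

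**Screening at delivery.** It appears in four other places:
- Study population and selection criteria, for controls: "patients with a negative COVID-19 delivery diagnosed by PCR screening at delivery, or less than 3 days before, were considered".
- Data collection, which lets sites bring in existing cohorts of women screened whatever the result.
- Substudy 3, Design, which relies on universal consecutive PCR screening.
- Substudy 4, Inclusion criteria, which takes women with no earlier positive test who have a PCR from 72 hours before to 24 hours after delivery.

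All four substudies are extracted from the one registry.

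**Timing variable and analysis.** The Substudy 2 variable table lists "COVID 19 diagnosis date" and symptoms reported at birth, and refers to Appendix 5 for the rest. Substudy 2, Statistics, summarises the included population and then tests associations. It mentions no division by how or when the infection was found.

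**The concern.** A distribution of gestational age describes the infection only if the chance of being detected is roughly the same throughout pregnancy. Here it is not. Before delivery, an infection that raises no suspicion and prompts no rule-out test is missed. At delivery, a screening site finds every woman who is still PCR-positive. Cases accumulate around delivery even if infection risk is flat, and the added cases are mainly women without symptoms.

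Two results are affected. The timing distribution could be read as infection clustering late in pregnancy. The percentages admitted to ICU, ventilated or dead depend on how many screen-detected women are in the denominator, so they can move with site and calendar period without any change in the disease. The protocol's background section discusses disease course by trimester, so readers are likely to use the result for that question.

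**Working it through.** **Nothing to reproduce.** The protocol states that no sample size was calculated for the clinical-course description and gives no expected detection rates. All inputs below are assumptions, so the results illustrate direction and rough size only.

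**Model 1. Inputs (assumed).** Constant infection risk over 40 weeks; PCR positive for w = 2 to 4 weeks; a share s = 0.15 to 0.50 of infections found on suspicion; delivery screening finds everyone still positive.

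Per 40 infections spread evenly over pregnancy, detected cases number w (last w weeks, either route) plus s(40 − w) (earlier, suspicion only). Then:
- A, share of detected cases infected in the last w weeks by either route = w / [w + s(40 − w)]
- B, share detected only by delivery screening = (1 − s) × A
- true share of infections in that window = w/40

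| w | s | A | True | A ÷ true | B |
|---|---|---|---|---|---|
| 2 | 0.50 | 2/21 = 9.5% | 5% | 1.9 | 4.8% |
| 3 | 0.30 | 3/14.1 = 21.3% | 7.5% | 2.8 | 14.9% |
| 4 | 0.15 | 4/9.4 = 42.6% | 10% | 4.3 | 36.2% |

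A and B rise with w and fall with s, so the outer rows give the limits.

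**ICU percentage under model 1.** Suppose also that every infection leading to ICU is among those found on suspicion.
- Against suspicion-detected women, the pooled risk is (1 − B) times theirs: 95.2%, 85.1% and 63.8% of it in the three rows.
- Against all infections, it is too high by 40 / [w + s(40 − w)]: 40/21 = 1.9, 40/14.1 = 2.8 and 40/9.4 = 4.3 times.

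The pooled figure lies between two meaningful risks and equals neither.

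**Model 2, a cross-check with severity.** Assume a symptomatic share p (0.2 to 0.8). Of symptomatic infections, 10% are severe and always detected, and the rest are tested with probability d (0.3 to 1.0). All infections in the last w = 2 or 3 weeks are caught. Earlier detection is q = 0.1p + 0.9pd, and the observed share in the window is w / [w + (40 − w)q].
- p = 0.5, d = 0.6, w = 3: q = 0.05 + 0.27 = 0.32, and 3 / (3 + 37 × 0.32) = 3/14.84 = 20.2%, against 7.5%.
- Over the grid, w = 3 gives 9.2% to 52.3% against 7.5%, and w = 2 gives 6.2% to 41.6% against 5%.
- Severe share of all detected cases (p = 0.5, d = 0.6): 0.05/0.32 = 15.6% earlier and 5.0% near delivery, with true severity constant.
- Among symptomatic women only, the contrast narrows to 15.6% against 0.05/0.5 = 10%. It disappears if every symptomatic woman is tested (d = 1).
- Check: with p = 1 and d = 1 the share is 7.5% and severity is 10% in both periods, so the distortion vanishes when detection does not vary.

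**The case against.** **Delivery screening is not stated for Substudy 2.** Its Patients section names suspicion and rule-out only. The screening text concerns controls, imported cohorts and Substudies 3 and 4. This stands as a qualification: the route is inferred. It is a reasonable inference, because the substudies share one registry, the case definition ignores symptoms, and nothing excludes women found by screening.

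**A split by route could be left to a statistical analysis plan.** One may exist and is not shown. However, the protocol already has a statistics section for this substudy and fixes both the target and the case set. Following it as written gives one summary.

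**The protocol covers part of the ground.** It defines symptomatic and asymptomatic groups, names symptomatic infection as a possible risk modifier, and grades WHO severity only in cases with a clinical presentation. A reader might infer that asymptomatic women dilute the severity grades; for the WHO grades the text does not support that. ICU, ventilation and death have no such restriction. The Heterogeneity tests section deals with differences between sites, whereas this problem arises within each site as gestation advances.

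**Onset may be recorded.** Appendix 5 and the COVID-19 diagnosis form are not shown, and the symptom-group definitions need symptom timing. A reader might infer that delivery dates will be used as onset dates; the protocol does not say so. An onset date would still not exist for asymptomatic women.

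**The size is assumed.** Correct. At the favourable end of model 2 (6.2% against 5%) the effect is small.

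**Conclusion.** The point holds as a defect in how Substudy 2 fixes its target and case set. Detection rises at delivery, so the timing distribution is inflated there and the pooled ICU and death percentages depend on the screening mix. The direction requires only that some infections earlier in pregnancy go untested and that women screened at delivery enter Substudy 2. The size rests wholly on the stated assumptions.

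Three stronger readings are not supported:
- **That 10 to 43% of cases would be diagnosed at delivery.** That range is the share infected in the last weeks and detected by either route. The share found only by the delivery screen is about 5 to 36%.
- **That ICU risk is simply understated.** This is so only against suspicion-detected women. Against all infections the pooled figure is too high under the same assumptions.
- **That cases pile up at term and asymptomatic infection enters almost only there.** The excess is at delivery, which includes preterm births, and rule-out testing is not limited to women with symptoms.

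The substudy is descriptive and no decision threshold hangs on it. The change is still worth making, because it alters what the results can be taken to show.

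**What to change.** In Substudy 2, Statistics:
1. Report all clinical-course results separately for (a) women diagnosed before delivery on suspicion or rule-out and (b) women first positive at delivery screening without earlier symptoms. Use the recorded reason for testing if there is one; otherwise use diagnosis date, delivery date and symptom status.
2. Restrict gestational age at onset to symptomatic women, dated by symptom onset where recorded. Label all other timing as gestational age at diagnosis.
3. State that group (b) reflects prevalence at delivery and not the timing of infection.

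**Cost.** No extra testing or recruitment: some analysis wording and one extra table. The groups become smaller. Where the reason for testing is not recorded, some women will be assigned to the wrong route, particularly as the symptoms listed in the main table are those reported at birth. Whether Appendix 5 holds the reason for testing and the onset date should be checked first.

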## Design

Descriptive Observational Study

Recruitment: 1st March 2020 to 1st March 2021. Spanish sites collected in Appendix 1.

## Patients

Patients eligible for follow-up or target population will be any pregnant woman who is suspected of or needs to be ruled out as having SARS-CoV-2 infection at any time during pregnancy with positive test results for SARS-CoV-2 by PCR.

The result in the PCR test on a sample of nasopharyngeal and/or oropharyngeal swab was considered synonymous with exposure/non-exposure, defining a case as any pregnant woman with a positive result, regardless of the symptoms. Those cases with clinical presentation of COVID19 were classified according to the WHO division for adults into: mild symptoms, mild-moderate pneumonia, severe pneumonia and septic shock (16).

The recommended samples for diagnosis are samples from the upper respiratory tract: nasopharyngeal and/or oropharyngeal swab.

## Primary variables

|                                                    |                                      |
|----------------------------------------------------|--------------------------------------|
| Age                                                | Premature rupture of membranes (PRM) |
| Race                                               | Preterm PRM                          |
| Weight at the beginning of pregnancy               | NICU admission                       |
| BMI: Body Mass Index                               | NICU admission days                  |
| Single or Multiple Gestation                       | APGAR 5                              |
| IVF with egg donation and IVF without egg donation | Arterial pH                          |
| Medical comorbidity                                | Postpartum haemorrhage               |
| Blood group and Rh                                 | Abruptio placentae                   |
| Maternal mortality                                 | Severe preeclampsia                  |
| ICU admission                                      | HELLP                                |
| Intrauterine foetal mortality                      | Pulmonary embolism                   |
| COVID 19 diagnosis date                            | Endometritis                         |
| Delivery < 37 weeks                                | Mastitis                             |
| Delivery Type                                      |                                      |

|                                                   |                                 |
|---------------------------------------------------|---------------------------------|
| COVID-19 symptoms                          |                                 |
| Mild symptoms (Symptoms reported at birth) | Cough                           |
|                                                   | Fever                           |
|                                                   | Dyspnoea                        |
|                                                   | New olfactory or taste disorder |
|                                                   | Fatigue/malaise                 |
|                                                   | Altered consciousness           |
|                                                   | Headache                        |
|                                                   | Nausea/vomiting                 |
|                                                   | Diarrhoea                       |
| Mild-moderate pneumonia                    |                                 |
| Severe pneumonia                           |                                 |
| Septic shock/maternal mortality            |                                 |

The rest of the variables are defined in appendix 5

## Statistics

For the statistical analysis, the SAS v9.4 software will be used.

The set of groups of variables requested and collected for each enrolled patient will be the same. The demographic and clinical characteristics of the population included will be summarized. Mean, standard deviation, minimum and maximum or median and interquartile intervals will be used for continuous variables, according to the distribution. The corresponding absolute and relative frequency will be reported for the discrete variables.

An analysis of the possible association of both the characteristics of the patients and the outcomes collected with COVID-19 infection will be carried out using Pearson's Chi-square test or Fisher's exact test and the Mann-Whitney U test (after verification of the absence of normal data by the Kolmogorov-Smirnov test). See section on Data Quality Plan and sample size. Statistical significance was established with  $P < 0.05$ . All statistical analyses were carried out with SAS 9.4 software.

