### Substudy 1: Prospective observational study on delivery and vertical transmission to the new-born.

#### Objective/s

1. Determine the variables that are associated with more maternal and neonatal morbidity.
2. Determine if there is vertical transmission.
3. Evaluate the risk of SARS-CoV-2 infection during pregnancy.
4. Characterize the clinical course of SARS-CoV-2 infection during delivery
5. Identify additional risk factors and risk modifiers (e.g., symptomatic infection, SARS-CoV-2 positive amniotic fluid, co-infections).

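### Substudies 1 and 2 enrol only PCR-positive women, but their only planned inferential analysis is a comparison by COVID-19 infection, so their morbidity risk-factor objectives have no usable analysis

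*Protocol*

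**What the plan says.** **Population.** In the Protocol, the Patients sections of Substudies 1 and 2 make eligible women who are suspected of infection, or in whom it must be ruled out, "at any time during pregnancy with positive test results for SARS-CoV-2 by PCR". Neither section mentions controls. The same sections make the PCR result the exposure variable: it "was considered synonymous with exposure/non-exposure, defining a case as any pregnant woman with a positive result, regardless of the symptoms". Substudy 2 is titled "Prospective observational study on maternal and neonatal morbidity in pregnant women with COVID-19" and its design is given as "Descriptive Observational Study".

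**Objectives.** Both substudies list "Determine the variables that are associated with more maternal and neonatal morbidity" and the identification of further risk factors and modifiers, with symptomatic infection as one example. Substudy 1 adds, as objective 3, "Evaluate the risk of SARS-CoV-2 infection during pregnancy".

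**Analysis.** Beyond descriptive summaries, each of the two Statistics sections contains one plan: "An analysis of the possible association of both the characteristics of the patients and the outcomes collected with COVID-19 infection will be carried out". The tests are Pearson's chi-square or Fisher's exact test, and Mann-Whitney U. "Statistical significance was established with" P < 0.05.

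**Controls.** The registry-wide section on study population and selection criteria provides for PCR-negative controls in the same database. The rule for sampling them (same site, deliveries adjacent to the case, at most 3 per case) appears only under Substudy 3.

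**The concern.** The grouping variable of the planned tests is the eligibility criterion of the cohort. Everyone in Substudies 1 and 2 is infected, so there is no second group to compare. Nearly the same sentence stands in the Statistics section of Substudy 3, where it fits because that substudy has PCR-negative controls, and a close variant stands in Substudy 4, which also includes PCR-negative women. In Substudies 1 and 2 it reads like carried-over text.

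At stake are the risk-factor objectives. They need morbidity as the response and patient characteristics as the explanatory variables, among infected women. Neither Statistics section states such a contrast. If the protocol is left as it is, the contrast would have to be chosen outside it, possibly after the data are seen, over many variables each tested at 0.05.

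**Working it through.** The protocol gives no sample size, event count or power for Substudies 1 and 2, so there is no figure to reproduce. The check is structural.

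**1. The tests in the population as defined.** Assume, for illustration only, 500 PCR-positive women, 60 with an outcome and 440 without, and 0 PCR-negative women. The result does not depend on these counts.

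- *Pearson chi-square.* Expected count = row total × column total / N. For the PCR-negative column this is 60 × 0 / 500 = 0 and 440 × 0 / 500 = 0, so each term (O − E)²/E is 0/0. With one non-empty column, degrees of freedom = (2 − 1)(1 − 1) = 0. The statistic is undefined; the software stops with an error about a zero expected frequency.
- *Fisher's exact test.* With a column total of 0, only one table fits the margins, so its probability is 1 and p = 1 for any data. The odds ratio is (60 × 0)/(440 × 0) = 0/0. The test is degenerate; run on these counts it gave an undefined odds ratio and p = 1.
- *Mann-Whitney U.* With n₁ = 500 and n₂ = 0, the null mean n₁n₂/2 = 0 and the null variance n₁n₂(n₁ + n₂ + 1)/12 = 500 × 0 × 501/12 = 0. The standardised statistic is 0/0; run, it returned no value.

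**2. The tests if the registry's controls are brought in.** Keep the 60/500 and add 1,500 controls (3 per case, the Substudy 3 maximum) with an assumed 80 events. Then χ² = N(ad − bc)²/(product of the four margins) = 2000 × (60 × 1420 − 80 × 440)² / (500 × 1500 × 140 × 1860) = 25.6 on 1 degree of freedom. The test now runs. What it compares is 60/500 = 12.0% in infected women with 80/1500 = 5.3% in uninfected women. That is Substudy 3's stated purpose. It says nothing about which of the 500 infected women were the 60.

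**3. Objectives set against the planned analysis.**

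| Objective | Contrast needed | Served by the Statistics section? |
|---|---|---|
| Substudy 1, no. 1; Substudy 2, no. 1: variables associated with morbidity | Morbidity present vs absent, among infected women | No |
| Substudy 1, no. 5; Substudy 2, no. 3: risk factors and modifiers | Same, by symptom status, co-infection and so on | No |
| Substudy 1, no. 3: risk of infection | Infected and uninfected women, on either reading | No |
| Substudy 1, no. 2: vertical transmission | Proportion of positive neonatal tests | Yes, by frequencies |
| Substudy 1, no. 4; Substudy 2, no. 2: clinical course | Frequencies and summaries | Yes |

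This leaves 3 of 5 objectives in Substudy 1 and 2 of 3 in Substudy 2 without a matching analysis: 5 of 8.

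**4. Whether another section fills the gap.** Substudy 3 fits logistic models for each outcome, but its Statistics section reports only the COVID odds ratio and sets the other covariates aside as adjustment variables. The section on heterogeneity tests mentions interaction terms and random intercepts, but refers back to regression models that do not appear before it and names no response variable for Substudies 1 or 2. The sections on data quality and sample size, to which both Statistics paragraphs point, define no contrast.

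**The case against.** The best defence is that all four substudies are extractions from one registry, that this registry is to hold PCR-negative controls, and that the Patients sections themselves speak of exposure and non-exposure. On that view the comparator is merely unstated. This stands in part: a reader might infer that the tests are impossible to compute, and the protocol does not support that once controls are extracted. It does not rescue the risk-factor objectives, as step 2 of the working shows.

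Second, Substudy 2 is labelled descriptive, the protocol says the clinical course is characterised without hypotheses, and no substudy names a main objective. This also stands. It would be too strong to say that either substudy loses its main result, because the descriptive objectives can be met as planned.

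Third, an analysis plan may exist that specifies the right models, and the choice of model and covariates normally belongs there. That is fair for the model. It does not cover a protocol sentence that fixes a specific contrast at odds with the protocol's own eligibility criteria: a plan that follows the sentence inherits the conflict, and one that departs from it sets the contrast outside the protocol.

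Fourth, Substudy 1 objective 3 can mean the risk of acquiring infection or the risk that infection poses. A reader might infer that it should be deleted. The wording does not justify that, although both readings need uninfected women.

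Finally, because the background links caesarean section with severe maternal illness, a reader might infer a confounded delivery-mode comparison. Neither Statistics section plans such a comparison, so that criticism has no object here.

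**Conclusion.** The point holds. In Substudies 1 and 2 the stated population and the only stated inferential analysis contradict each other, and no other section reconciles them. As written, two of the three named tests are undefined and the third always gives p = 1. With the registry controls added, the tests answer a different substudy's question. Two of the four substudies are affected, and within them five of eight objectives; vertical transmission and clinical course are not affected.

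The conclusion rests on reading the two Patients sections literally, as PCR-positive women only, and on the absence of any control group in them. The illustrative counts in the working carry no weight in it. It does not extend to a claim that the registry cannot support these objectives: suitable outcomes and characteristics are already listed.

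**What to change.** - **Statistics sections of Substudies 1 and 2.** Replace the comparison by COVID-19 infection with a contrast among infected women that matches the risk-factor objectives: maternal morbidity (for example ICU admission, severe pneumonia, septic shock or death) and neonatal morbidity (for example NICU admission), each present versus absent, against the listed maternal characteristics, comorbidity and symptom status. The protocol grades pneumonia and septic shock only among women with clinical COVID-19, so symptom status is tied by definition to those outcomes and is informative mainly for the others.
- **Patients sections of Substudies 1 and 2.** If a comparison with uninfected women is also intended, state that the registry's PCR-negative controls are included. This adds to the within-case contrast and does not replace it.
- **Substudy 1, objective 3.** Say which risk is meant, and either name the uninfected comparator or move the objective to Substudy 3 or 4.

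The cost is rewording two paragraphs and one objective, plus one sentence in each Patients section if controls are wanted. The example outcomes and predictors are in the Substudy 2 variable list. Substudy 1's own table lacks NICU admission and comorbidity; the registry-wide section on data collection covers the first, and the section on study population and selection criteria covers the second. The model and the covariate set can be left to the analysis plan.
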